#### Qualitative study

In qualitative research, the sample size needs to enable rich and diverse data to be collected to provide valuable insights about the topic of interest and to be sufficient to generate an in-depth understanding of it [53]. Based on this information, we have estimated that around 12 to 15 participants may be necessary to reach the qualitative purposes of this study.

### Data analysis

#### Pilot RCT

Baseline demographics will be described using means and percentages and their standard deviations. Primary feasibility outcomes will be analysed using percentages (proportions) and 95% confidence intervals (CIs). Patient-reported outcome measures—including physical function, anxiety, depression, fatigue, sleep disturbance, ability to participate in social roles and activities, pain interference, pain intensity, chronic pain acceptance and mindfulness adherence—will be analysed using between-group comparisons based on intention-to-treat principles Given the exploratory nature of this pilot study, we will report mean differences with 95% confidence intervals to describe potential trends and variability in the data. Quantitative analysis will focus on estimating effect sizes and variability, which will help guide the design and sample size calculation of a future full-scale trial. This approach aligns with best practices for pilot studies, ensuring that the findings are used primarily to inform the feasibility and refinement of the intervention [54].

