##### Patient-reported outcome measures (PROMs)

Upon entry to the study, prior to randomisation, we will collect demographic information, including age, gender, race, ethnicity, education level, and postcode (to be used as a proxy for socioeconomic status). We will also collect information about the participant’s general health status and pain condition, including the number of years they have lived with chronic pain and their primary sources or locations of pain. Patient-reported outcome measures will be collected upon entry to the study prior to randomisation, and at the conclusion of the online MBSR program, to assess preliminary pre- to post-intervention changes. We will use the validated and widely used patient-reported outcome measures that make up the electronic Persistent Pain Outcomes Collaboration (ePPOC). The ePPOC is a resource for pain researchers and clinicians, which was established in NSW in 2013, to evaluate and assist in improving outcomes and services for people experiencing chronic pain [41]. The ePPOC measures pain and disability using the Brief Pain Inventory (BPI) [42], cognition using the Pain Self-Efficacy Questionnaire (PSEQ) [43], pain catastrophising using the Pain Catastrophising Scale (PCS) [44], mood using the Depression, Anxiety and Stress Scale (DASS-21) [45], health care utilisation and medication. These measures are recommended and used in pain management centres within Australia and New Zealand. We will also measure chronic pain acceptance using the Chronic Pain Acceptance Questionnaire (CPAQ) [46]. The CPAQ measures two aspects of chronic pain acceptance - activity engagement and pain willingness. Participants will be emailed a link to these questionnaires, which will be embedded into a web-based application (REDCap). The data collection process is illustrated in Fig. 2.

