##### Adherence to the mindfulness practice

Adherence to the suggested daily mindfulness practices throughout the 8-week intervention will be measured weekly via REDCap, using an online version of the Mindfulness Adherence Questionnaire (MAQ) [47]. The MAQ is a 12-item self-reported questionnaire that captures adherence to the mindfulness practice within the past week. It was designed to assess regular and sustained practice in attentional focus and non-judgmental acceptance (i.e. quantity, quality, subtype of practice). The first two items measure the frequency and average duration (in minutes) of formal practices. The remaining 10 items measure the quality of formal practice and informal practice. Items are scored on a 7-point Likert scale ranging from 0 (never) to 6 (always), with higher total subscale scores reflecting higher practice quality.

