### Sample size

#### Pilot RCT

Decisions about sample size in pilot studies can be challenging as a variety of approaches exist [49–52]. Some researchers suggest that pilot studies should include at least 30 participants to provide a reliable estimate of the standard deviation, which is essential for calculating the sample size of a future full-scale trial [51]. Based on these guidelines, we plan to recruit 32 participants (approximately 16 per group) for this pilot study. This represents 9% of the estimated sample size for the full trial, which is the minimum threshold recommended by Cocks and Torgerson (2013) [50]. This sample size provides >80% confidence in determining whether to proceed with a full trial, aligning with feasibility objectives. The calculation is based on an estimated effect size difference for the full trial, using a confidence interval approach [50]. A key feasibility outcome is the retention rate, which we anticipate to be 80%. Given our sample size (*N*= 32), this can be estimated to be within approximately ±15% with 95% confidence, meaning that around 26 participants are expected to complete the study [39]. However, we acknowledge that this estimate is provisional and will be refined based on feasibility data collected from the pilot study, including actual retention rates, standard deviation estimates, and adherence metrics.

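### The planned mean differences for the patient-reported outcomes make no stated use of the baseline scores and do not say whether they compare final scores or changes

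*Protocol article*

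**What the plan says.** The Data analysis section (Pilot RCT) lists the patient-reported outcomes and says that they "will be analysed using between-group comparisons based on intention-to-treat principles". It then gives the effect measure: "we will report mean differences with 95% confidence intervals to describe potential trends and variability in the data". The section mentions baseline only to describe demographics. No model, covariate or change score is named for the PROMs anywhere in the article.

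The section on PROMs gives the timing: "Patient-reported outcome measures will be collected upon entry to the study prior to randomisation, and at the conclusion of the online MBSR program". The same sentence gives the purpose: "to assess preliminary pre- to post-intervention changes".

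Not every listed outcome has a baseline. The list ends with "chronic pain acceptance and mindfulness adherence", and adherence to practice "throughout the 8-week intervention will be measured weekly via REDCap", so it has no value before randomisation. Fatigue, sleep disturbance and participation in social roles are also listed, but the PROMs section names no instrument for them.

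On numbers, the Sample size section says "we plan to recruit 32 participants (approximately 16 per group) for this pilot study". It expects 80% retention, "meaning that around 26 participants are expected to complete the study".

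**The concern.** A baseline score measured on the same scale is usually the strongest available predictor of the follow-up score. In a trial with 13 to 16 people per arm, it does two things when used as a covariate. It removes the part of the outcome variance that baseline explains, and it corrects the estimate for whatever baseline difference the randomisation happened to produce. A between-group mean difference taken at face value does neither.

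The text also leaves two unadjusted quantities open. The Data analysis section does not say what the mean difference is a difference of, while the PROMs section speaks of change. These estimators have different variances and carry baseline imbalance in opposite directions. If the choice is not fixed in advance, it can be made after the data are seen.

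The article says that the quantitative work will concentrate on effect sizes and variability to help plan the full trial. The SD of final scores, the SD of changes and the residual SD after adjustment are different planning inputs. A mean difference with its interval does not show how they relate, because it does not give the baseline to follow-up correlation.

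**Working it through.** **The plan's own figures.** The article gives no interval width for the PROMs. Its only precision figure is for retention. 0.80 × 32 = 25.6, about 26 completers. The Wald half-width is 1.96 × √(0.80 × 0.20 / 32) = 13.9 points, or 15.4 with the continuity correction 1/64. The stated figures of about 26 and about ±15% are reproduced. With 1:1 allocation, 26 completers means about 13 per arm.

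**Inputs.** n = 16 per arm (all randomised) or 13 per arm (expected completers), both from the Sample size section. Results are in units of the outcome SD. The baseline to follow-up correlation r is not in the document; it is assumed and varied.

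**Formulas for the 95% half-width.**
- Final scores: t(2n−2) × √(2/n)
- Changes: t(2n−2) × √(2/n × 2(1−r))
- Baseline-adjusted (ANCOVA): t(2n−3) × √(2/n × (1−r²) × (1 + 1/(2n−4))). The last factor is the average small-sample cost of estimating the slope.

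**Example, n = 13, r = 0.5.** Final scores: 2.064 × √(2/13) = 0.81. Changes: 2.064 × √(2/13 × 1.0) = 0.81. Adjusted: 2.069 × √(0.1538 × 0.75 × 1.0455) = 0.72.

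| r (assumed) | Final, 13/arm | Change, 13/arm | Adjusted, 13/arm | Final, 16/arm | Adjusted, 16/arm |
|---|---|---|---|---|---|
| 0 | 0.81 | 1.14 | 0.83 | 0.72 | 0.74 |
| 0.2 | 0.81 | 1.02 | 0.81 | 0.72 | 0.72 |
| 0.3 | 0.81 | 0.96 | 0.79 | 0.72 | 0.70 |
| 0.5 | 0.81 | 0.81 | 0.72 | 0.72 | 0.64 |
| 0.7 | 0.81 | 0.63 | 0.59 | 0.72 | 0.53 |
| 0.8 | 0.81 | 0.51 | 0.50 | 0.72 | 0.44 |

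Compared with final scores, adjustment narrows the interval by 2–3% at r = 0.3, 11–12% at r = 0.5 and 27% at r = 0.7. It breaks even at about r = 0.2 and is 1–3% wider at r = 0 to 0.1. A change-score difference is 18% wider than a final-score difference at r = 0.3, equal at 0.5 and 23% narrower at 0.7. Over the range examined it is never narrower than the adjusted one.

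**Chance imbalance.** The SD of the baseline difference between arms is √(2/16) = 0.35 SD, or √(2/13) = 0.39 SD. The probability that it exceeds 0.5 SD in either direction is 16% or 20% for each outcome. Only a fraction r of it enters a final-score difference. With 16 per arm and r = 0.5, the 95% range of imbalance is ±1.96 × 0.354 = ±0.69 SD, of which about ±0.35 SD is carried into the estimate. A change-score difference carries r − 1 times the imbalance, which is the opposite sign.

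**Simulation (8,000 runs per setting, no true effect).** With 13 per arm, the mean half-width was 0.80 for final scores, and 0.78, 0.71 and 0.59 adjusted at r = 0.3, 0.5 and 0.7. The slope of the estimate on the baseline imbalance was 0.31, 0.51 and 0.71 for final scores and 0.01 or less for the adjusted estimate. Both estimators averaged zero to within 0.005 in every setting.

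**The case against.** The strongest reply is that the article does not specify an unadjusted analysis at all. A coefficient from a baseline-adjusted model is also a mean difference with a 95% interval. A condensed article commonly leaves the covariates to an analysis plan, and any such plan is not shown here. This stands in part: a missing model statement alone would be no finding. What remains is that the article does name its effect measure, in a form that mentions no baseline score and leaves final score or change undecided.

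Four stronger readings are tempting, and the text does not support them:

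- **The plan prescribes plain differences of post-treatment scores.** It says neither, and the PROMs section points towards change.
- **Every outcome has a baseline.** Mindfulness adherence has none, and for three other listed domains no instrument is named from which to tell.
- **The PROM analysis is confined to the 26 or so completers, against intention-to-treat.** Nothing restricts it in that way. Nor would ANCOVA on observed outcomes answer that complaint, because it too omits people without a follow-up score.
- **An unadjusted difference is biased.** It is not biased over repeated randomisation, and its interval already allows for chance imbalance. The argument for adjustment is precision, and accuracy given the allocation actually obtained.

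It is also fair that the gain depends on an unknown correlation and is negligible at 0.3 or below.

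**Conclusion.** The point holds as a low-severity improvement to the specification. Adjustment for the baseline score does better than both unadjusted readings once the correlation exceeds about 0.2. The gain becomes material from about 0.5, where the half-width with 13 per arm falls by about 0.09 SD, and at 0.7 it falls by about 0.22 SD.

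These sizes assume equal arms, a common SD at both time points and across arms, a linear relation, and a correlation that the article does not give. The consequence is limited: progression is decided on retention, and the article itself asks for caution with the PROM results. What is affected is the quality of the effect and variability estimates passed to the full trial.

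**What to change.** In the Data analysis section, replace the general reference to mean differences with wording such as: *Each patient-reported outcome with a pre-randomisation score will be compared between groups by a linear model adjusted for the baseline value of the same measure. We will report the adjusted mean difference with its 95% confidence interval, the raw SD and the baseline to follow-up correlation. Outcomes without a pre-randomisation value, such as mindfulness adherence, are not included in this adjustment.*

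A mixed model over the two time points with a common baseline mean is an acceptable alternative. It also uses the baseline scores of randomised participants who have no follow-up score. The authors should list which outcomes have a baseline, since this is unclear for fatigue, sleep disturbance and social participation.

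Reporting the raw SD and the correlation r lets the planners of the full trial obtain the residual SD as raw SD × √(1−r²). The pilot's estimate of r will itself be imprecise, so a range should be carried forward.

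The cost is a few sentences and one degree of freedom per model, with the 1–3% widening shown above if the correlation is near zero. No new data are needed.

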#### Qualitative study

Qualitative interview data will be analysed using reflexive thematic analysis [55], with the assistance of NVivo software. The Coordinating Principal Investigator and the interviewer will jointly conduct the thematic analysis of the transcripts supervised by an experienced qualitative researcher. Contextual themes will be identified in the data and supported by quotes. All members of the research team will provide input into the results and will be encouraged to engage in reflexivity as part of the analytical process (i.e. reflect on their reactions to the data, how their positionality may influence their interpretation, their motivations to engage in such research, and more). Rigour will be guided by Braun and Clarke’s recommendations for reflexive thematic analysis [55]. The qualitative findings will be integrated with the quantitative results to provide a richer understanding of feasibility outcomes, such as adherence rates and participant-reported experiences. Thematic analysis of the qualitative data will be conducted after quantitative analysis, allowing for triangulation of findings and identification of factors that may influence intervention engagement and effectiveness [55].

### Ethics

This pilot RCT includes key methodological features to minimise bias in clinical trials, such as randomisation, concealed allocation, specification of eligibility criteria, blinded outcome assessment, blinded analysis, and intention-to-treat analysis. Data will be stored in spreadsheets and transferred to appropriate statistical software for analysis by an investigator blinded to group allocation. Spreadsheets will be regularly scrutinised for omissions and errors. Data will be stored and accessed as per the ethics requirements.

We will adhere to the Australian Code for the Responsible Conduct of Research for the storage and archiving of data. Data will be retained for 5 years with restricted access (the research data and/or metadata cannot be shared). All data files (e.g. audiotapes, transcripts) will be stored on a secure server at The University of Sydney, with access restricted to the study investigators. Data files will be coded. After 5 years of storage, the data will be securely destroyed. Electronic data will be deleted, and any paper copies will be shredded.

A Data Safety Monitoring Board (DSMB) will be convened to oversee this study. The board will be comprised of three members: an Associate Professor who is a psychologist, an Associate Professor who is a physician, and a senior physiotherapist who is the Director of Allied Health Services at one of the Sydney Local Health Districts and Co-Chair of the Musculoskeletal Network at the Agency of Clinical Innovation. The DSMB will have an initial meeting before the study commences. In this initial meeting, the DSMB will review the role and functioning of the DSMB, discuss the format and content of the DSMB reports and review scientific and ethical issues relating to the design and conduct of the trial. The DSMB will meet again at 4 weeks after the MBSR program commences and at the end of the 8-week program.

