Potential participants who expressed interest in the study over the phone with one of the Clinical Nurse Consultants who did not complete the pre-screener survey will be sent a reminder email 3 to 5 days after the initial email. The reminder email will also mention that a research investigator may contact potential participants on their provided phone number to see if they have received this email and if they are still interested in learning more about the study.

If potential participants do not complete the pre-screener survey after the reminder email, a research investigator will call them 1 week after the initial contact from the Clinical Nurse Consultants to ask if they have received the email and if they are still interested in learning more about the study. This will be the last attempt to contact the participants. No further contact will be made if they are not interested. During the call, if they remain interested in the study, the research investigator will direct the potential participants to the email or re-send the email with the Participant Information Sheet, Consent Form and the pre-screener survey. Potential participants will also have the opportunity to ask questions about the study during the phone call.

If a potential participant who received a recruitment SMS and did not opt out of future communications about the study does not complete the pre-screener survey, they will be sent a follow-up SMS 5 days after the initial SMS. This will be the last attempt to contact the participants. No further contact will be made if they are not interested.

If eligible after completing the pre-screener survey, potential participants will receive a phone call from an experienced MBSR teacher and psychotherapist to screen for mental health concerns. During the phone call, the MBSR teacher will ask eleven questions to screen for any severe and uncontrolled mental health condition or a history of an unexplored, untreated traumatic experience. If eligible after completing the mental health screen, potential participants will be reminded that if they agree to participate in the study, they have a 50% chance of being in either the MBSR group or the usual care control group.

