### Intervention

Participants will be randomised into one of two parallel groups: (1) an online live facilitated MBSR group or (2) a usual care control group.Participants in the online live facilitated MBSR group will participate in an 8-week intervention involving weekly 2.5-h online group sessions and one online half-day workshop. This 6-h workshop, called “The Day of Mindfulness”, will be scheduled between the sixth and seventh week, and is held in silence with only the instructor speaking. This “retreat” will provide participants with an opportunity to deepen what they learn during the weekly online sessions. Participants will be encouraged to practice mindfulness daily throughout the 8-week period. In addition, participants will receive access to a 100-page coursebook, and a mobile application called *Openground Mindfulness Training* which has pre-recorded guided meditation practices that participants can use throughout the program. Patient data and app usage data will not be sent to the mobile application developer. Participants will also receive ongoing individual support from the MBSR teacher, as necessary.

Mindfulness is defined as non-reactive awareness of the present experience, including body sensations, internal mental states, thoughts, emotions, impulses and memories [20]. Mindfulness meditation is a mind training approach that cultivates cognitive control, emotion regulation and acceptance (i.e. nonreactivity), which leads to reduced stress and increased well-being [20]. During the online MBSR program, participants will meet once a week for 2.5 h via an online platform to practice mindfulness meditation and body awareness. During this time, the participants will also interact with each other through discussions facilitated by a skilled, certified MBSR teacher. Our proposed mindfulness intervention is based on MBSR, but it has been adapted for individuals with chronic pain. This program integrates psychoeducation on the latest pain neuroscience based on the evidence-based Explain Pain program [36, 37]. Each week, the teacher presents the theoretical underpinnings of the mindfulness training and the application of self-regulatory skills and encourages dialogue and reflection on distinct topics as described in Table 1 below.

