### Study limitations

While this pilot study aims to assess the feasibility of an online MBSR intervention for individuals with chronic musculoskeletal pain, some limitations should be acknowledged. Selection bias may arise due to the requirement for English proficiency and internet access, potentially excluding individuals from lower socioeconomic backgrounds. This limitation will be explicitly discussed in the study’s findings interpretation, and future research should explore strategies to enhance accessibility, such as translated materials and mobile-based adaptations. The small sample size limits generalisability, as pilot studies are not powered to detect definitive treatment effects. Differences in engagement between online and in-person MBSR programs may also impact adherence, as digital interventions often experience higher attrition rates [56]. To mitigate this, we will implement structured reminders, participant check-ins, and engagement tracking. Additionally, expectation-related bias may influence adherence, as participants’ perceptions of treatment effectiveness can shape engagement levels [57]. To address these challenges, both groups will receive clear information on the exploratory nature of the study and its contribution to chronic pain research. Despite these limitations, this study will generate valuable feasibility data to refine the intervention and inform a larger-scale trial.

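### The protocol claims blinded outcome assessment, but its patient-reported, practice-adherence and adverse-effect measures are completed by participants who know their arm

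*Protocol article*

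**What the plan says.** The Ethics section of the protocol article gives a list of safeguards against bias: "randomisation, concealed allocation, specification of eligibility criteria, blinded outcome assessment, blinded analysis, and intention-to-treat analysis". Assessment and analysis appear there as two separate blinded steps. The same paragraph then explains only the second, saying that the data will be "transferred to appropriate statistical software for analysis by an investigator blinded to group allocation".

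The measures themselves are described under Outcome measures:

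- **Patient-reported outcomes.** "Participants will be emailed a link to these questionnaires, which will be embedded into a web-based application (REDCap". They are "collected upon entry to the study prior to randomisation, and at the conclusion of the online MBSR program".
- **Practice adherence.** "Adherence to the suggested daily mindfulness practices throughout the 8-week intervention will be measured weekly via REDCap", with a self-report questionnaire.
- **Adverse effects.** A meditation-related adverse-effects scale reaches participants each week as an emailed REDCap link.

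The Intervention section defines the arms as "1) an online live facilitated MBSR group or (2) a usual care control group". Before enrolment, the Pre-screening section has potential participants reminded that "they have a 50% chance of being in either the MBSR group or the usual care control group".

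Under Study limitations, the article says that "expectation-related bias may influence adherence". It does not apply the same reasoning to the answers participants give about pain, mood or self-efficacy.

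**The concern.** When a participant completes a questionnaire about his or her own symptoms, the participant is the outcome assessor. Assessment is then blinded only if the participant is blinded. Here one arm attends weekly live group sessions for 8 weeks plus a 6-hour workshop, and the other continues with what waitlisted patients usually receive. There is no sham or attention control, so participants cannot be unaware of their arm.

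Two things are at stake. First, a reader who takes the Ethics section at face value will credit the preliminary efficacy results with a protection they lack. Second, the Data analysis section says that estimated effect sizes and variability will help guide the design and sample size of the full trial. If expectation shifts the reported outcomes towards MBSR, the estimated effect is too large, and a trial sized on it would be too small.

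**Working it through.** The plan states no figure on this point, and no calculation settles it. The check matches each outcome to its source and asks whether that source knows the allocation.

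| Outcome | Who supplies the value | Does the source know the arm? |
|---|---|---|
| Patient-reported outcomes at baseline | Participant, online | No: collected before randomisation |
| Patient-reported outcomes at the end of the program | Participant, online | Yes |
| Practice adherence, weekly | Participant, online | Yes |
| Adverse-effect scale, weekly | Participant, online | Yes |
| Recruitment and retention | Trial records | Does not depend on a symptom report |

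**Step 1: do participants know their arm?** The article does not say so in as many words, so this is an inference. It rests on three statements: both arms are named to them before enrolment, they are asked for a preferred session time in case they are allocated to MBSR, and the arms then differ by a live taught course. Offering the control arm an online educational resource does not disguise this, because the article lists that resource as part of usual care.

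**Step 2: is there any other assessor?** None is described for the patient-reported, adherence or adverse-effect measures. The teacher who telephones participants reporting impairing distress delivers the program and so knows who is in it. The qualitative interviewers are independent of the program, but they interview only MBSR participants, so independence there is not blinding to allocation.

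**Step 3: could the phrase mean the blinded analyst?** The list in the Ethics section names blinded analysis as a separate item, so the assessment claim must refer to something else, and nothing in the article supplies it.

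**Step 4: do the measured differences feed a decision?** The Data analysis section compares patient-reported outcomes between groups as mean differences with 95% confidence intervals, and uses effect sizes to guide the full trial. Write the true standardised difference as d and the shift due to unblinded reporting as b. The pilot then estimates d + b. The required sample size is proportional to 1/(effect)², so a trial sized on d + b would have (d/(d + b))² of the participants it needs. This ratio is below 1 whenever b has the same sign as d. The documents give neither d nor b, so the shortfall cannot be put in numbers. The confidence intervals reflect sampling error only and do not reveal b.

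**The case against.** Unblinded self-report is hard to avoid when live MBSR is compared with usual care, so the design itself is not at fault. The article is also cautious. It calls the analysis exploratory, asks that patient-reported results be read with care, notes that pilots are not powered for definitive effects, and plans to tell both groups that the study is exploratory. The Sample size section lists retention, standard deviations and adherence as the data that will refine the full-trial estimate, and does not list the effect size. All of this stands and lowers the consequence. It does not remove it: the stated reasons for caution are small numbers and preliminary status, not unblinding, and the Data analysis section does name effect sizes as input to the full trial.

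Two stronger readings are tempting, and the documents do not support them.

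- A reader might infer that every outcome is self-reported. The primary outcomes concern feasibility. Recruitment and retention come from trial records, and the progression rule (80%, 60% and 40% retention) does not use symptom reports.
- A reader might infer that blinded analysis fails too, because practice data would reveal the arms. The adherence section does not say which arm receives the questionnaire, and the Data analysis section lists mindfulness adherence among the between-group comparisons. The Ethics section provides for a blinded analyst and coded files. How the analyst's file is prepared is commonly left to documents not shown here.

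**Conclusion.** The claim of blinded outcome assessment contradicts the article's own description of how the clinical measures are collected. It is a misstatement to correct, not a flaw that calls for redesign. It applies to every post-randomisation patient-reported, practice-adherence and adverse-effect measure, and so to every between-group comparison of patient-reported outcomes. The likely direction of bias favours MBSR; its size cannot be derived from the documents. The feasibility decision and the blinded-analyst provision are not affected.

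The conclusion rests on one inference, that participants know their arm, which the design makes safe. It does not depend on anything that an unseen analysis plan might add, because the fault lies in a positive statement and not in an omission.

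**What to change.** 1. In the Ethics section, delete blinded outcome assessment from the list and add: *Patient-reported outcomes, practice adherence and adverse effects are self-reported by participants who are aware of their allocation; only the analyst is blinded.* The sentence should name these measures and not say all outcomes, which would be wrong for recruitment and retention.
2. Under Study limitations, extend the expectation-bias point from adherence to the between-group differences in patient-reported outcomes. State that these estimates may be biased, probably in favour of MBSR, and should not be taken at face value when the full trial is sized.

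The changes are to wording only. Data collection, participant burden and the feasibility criteria stay as they are. The cost is a less favourable statement of the trial's protection against bias.
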